**Methods/design:**

This study is a multicenter, double-blind, randomized controlled trial. A total of 640 DPN patients will be recruited and randomized to receive a foot bath with either the TW decoction or control drug. Participants will be assessed at baseline and 12 and 24 weeks after treatment. The primary outcome was the change of the Toronto Clinical Scoring System (TCSS). Secondary outcomes were nerve conduction velocity, blood glucose, blood lipids, serum inflammatory cytokines, and the European Quality of Life Five-Dimension Scale (EQ-5D) and TCM symptom scores.

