## Methods/design

### Study design

The protocol was designed according to Standard Protocol Items: Recommendations for Interventional Trials (SPIRIT) 2013. For the SPIRIT 2013 Checklist, see Additional file 1. This trial was registered at the Chinese Clinical Trial Registry (ChiCTR-IOR-16009331) and any significant protocol changes were revised accordingly. The prospective trial was designed following the principles of multicenter, double-blinded, and was controlled at a randomization of 1:1. The aim was to evaluate the therapeutic efficacy and safety of TW foot baths for DPN treatment. Patients who agree to participate in the study will be asked to provide written informed consent. Patients will be randomly allocated to either the TW experimental group or the control group after attending an educational session related to the clinical study. Patients will receive a foot bath for half an hour once a day (daytime and night are both acceptable) for two weeks and then stop for two weeks; this cycle constitutes a therapeutic course. All patients will be required to visit their clinicians every two weeks to be evaluated. If their Toronto Clinical Scoring System (TCSS) scores are < 6 points, the foot baths will be terminated and the patients will be followed up. If the TCSS scores are > 6 points, patients will receive a total of three therapeutic courses and then be followed up. All patients will be followed for three months after treatment. During the follow-up period, patients will be required to stop the foot baths and visit their clinicians monthly. Patients who drop out due to side effects or personal reasons will be also followed up. The flow chart of the trial is outlined in Fig. 1.

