### Eligibility criteria

Patients will be identified and selected by their clinicians based on their TCSS. The inclusion criteria are as follows: men or women aged 18–75 years; a diagnosis of DPN (no limitation on the degree of DPN) [22]; agreement to comply with the clinician’s treatment plan; TCSS scores of ≥ 6 points [23, 24]; and ability to understand and complete the informed consent process and consent to participate in the study.

The exclusion criteria are as follows: other neuropathies such as cervical or lumbar lesions (nerve root compression, spinal stenosis, cervical and lumbar degeneration), cerebral infarction, Guillain-Barre syndrome, or severe arteriovenous vascular lesions (venous thrombosis, lymph tube inflammation); lower extremity skin ulcers or gangrene, lower extremity edema, or suffering from skin diseases; diabetic ketoacidosis, hyperglycemia hypertonic syndrome, diabetes lactic acidosis, and other acute complications; patients with malignant tumors or severe dysfunction of the heart, liver, and kidneys; pregnancy or breast-feeding; participation in other similar interventions; mental disorders that render the patient unable to understand the nature of the study, its scope, and possible outcomes or unable to follow the doctor’s advice.

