### Statistical analysis

A statistician blinded to the patient allocation for each group will perform all analyses using PASW Statistics 17.0 software. Statistical analysis will be performed on an intention-to-treat (ITT) basis with 95% CI. The ITT analysis will include all randomized patients. All data will be presented as mean ± standard deviation and compared between groups using unpaired Student’s *t*-tests. Comparisons within a group will be performed using analysis of covariance. Count data will be analyzed using chi-square tests. Repeated measure ANOVA will be performed to assess the changes within and between groups over time. Subgroup analyses will be performed according to the treatment periods. *P* < 0.05 will be considered statistically significant.

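### If the planned subgroups by treatment period mean length of treatment received, they are formed after randomisation by the patient's own TCSS, and comparing arms within them is biased

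*Protocol article*

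**What the plan says.** The protocol article, Statistical analysis, gives subgroups one sentence: "Subgroup analyses will be performed according to the treatment periods". It names no other subgroup factor and does not say what a treatment period is.

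Study design explains how treatment length comes to differ between patients. Baths are taken daily "for two weeks and then stop for two weeks; this cycle constitutes a therapeutic course", so the maximum of three courses lasts 12 weeks. "All patients will be required to visit their clinicians every two weeks to be evaluated". Where TCSS "scores are < 6 points, the foot baths will be terminated and the patients will be followed up". Otherwise: "If the TCSS scores are > 6 points, patients will receive a total of three therapeutic courses and then be followed up". Entry requires "TCSS scores of ≥ 6 points".

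Treatment can also end or be interrupted for adverse events (Adverse events section) or through drop-out, including for personal reasons (Study design). The Abstract names change in TCSS as the primary outcome. Sample size expects falls of 3.5 points on TW and 1.5 on control. The main analysis is by intention to treat in all randomised patients.

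**The concern.** A subgroup is a set of patients, and the feature of treatment that Study design allows to differ between patients is how long they bathe. Read that way, the subgroup factor is decided after randomisation by the scale that serves as the primary outcome. If TW works as Sample size assumes, TW patients cross the threshold sooner and more often. Patients who stop after one or two courses are then differently selected in the two arms, and so are those who go on to three.

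A TW–control difference within such a stratum mixes the treatment effect with differences in baseline severity and in natural improvement. An effect that is the same for everyone would look smaller in the strata and uneven across them, and that unevenness could be misread as information about treatment duration.

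**Working it through.** **Is there a plan figure to reproduce?** No. The protocol states no number for the subgroup analysis, and Sample size gives no SD. The size below therefore rests on assumptions; the direction follows from the stopping rule.

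**Inputs from the protocol article.** Entry at TCSS 6 or more; assessment every two weeks; baths end at TCSS below 6; otherwise three courses (12 weeks); expected difference 3.5 − 1.5 = 2.0 points.

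**Assumptions, not in the document.** Underlying baseline TCSS has mean 9 or 10 and SD 2 or 3 before the entry filter. Natural 12-week improvement has mean 1.5 and between-patient SD 1, 2 or 3, and accrues linearly. Measurement SD is 1. Every TW patient gains exactly 2.0 points more than under control, and stopping does not alter the week-12 outcome. A score of exactly 6 continues treatment; the article assigns it to neither rule.

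**Method.** Simulate 400,000 patients per scenario, randomised 1:1, and apply the stopping rule at each visit. A stop at week 2 or 4 counts as one course, at week 6 or 8 as two, and a stop at week 10 or no stop as three. Because the true effect is 2.0 for everyone, any shortfall within a stratum is selection.

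**One scenario in full** (baseline mean 10, baseline SD 3, improvement SD 2):

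| Courses | Share TW / control | Mean baseline TCSS TW / control | Mean natural improvement TW / control | Apparent difference |
|---|---|---|---|---|
| 1 | 11.0% / 7.1% | 7.08 / 6.86 | 2.33 / 2.39 | 1.83 |
| 2 | 13.6% / 6.8% | 8.37 / 7.82 | 2.70 / 3.12 | 1.50 |
| 3 | 75.4% / 86.1% | 11.37 / 11.00 | 1.16 / 1.29 | 1.87 |
| All randomised | | | | 2.01 |

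The two-course row shows the mechanism. Control patients there start 8.37 − 7.82 = 0.55 points lower and would have improved 3.12 − 2.70 = 0.42 points more without TW. Natural improvement alone takes the apparent effect from 2.0 to 2.0 − 0.42 = 1.58. The other 0.08, down to 1.50, comes from baseline measurement error, which is also selected differently in the two arms.

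No weighting of 1.83, 1.50 and 1.87 can return 2.01, because all three lie below it. Strata fixed before randomisation would not behave this way beyond chance.

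**Range over eight scenarios with a true effect of 2.0:**

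| Comparison | Apparent difference |
|---|---|
| One course | 1.68–1.87 |
| Two courses | 1.27–1.72 |
| Three courses | 1.68–1.96 |
| All randomised | 1.99–2.01 |

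The shortfall runs from 2.00 − 1.96 = 0.04 to 2.00 − 1.27 = 0.73 points.

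**No treatment effect** (same assumptions as the full scenario): stratum differences are −0.04, −0.02 and 0.00, which is zero within simulation error.

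**The case against.** The strongest reply is that the phrase may not mean duration at all. The article uses the word period for trial phases: the follow-up period, the study period and, under Blood glucose, the end of the treatment period. The unit that varies with response is called a therapeutic course. If the sentence means treatment phase against follow-up in all randomised patients, this selection does not arise. That stands, and it makes the point conditional. It does not clear the sentence: a contrast between phases is a time-point comparison, which the repeated-measures ANOVA named just before it already covers, and calling it a subgroup analysis invites the harmful reading.

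Three stronger readings are tempting, and the documents do not support them.

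- *The subgroup analysis will show a steep gain with more courses.* A simulation in which improvement freezes when baths stop gives 0.39–0.48, 0.70–0.98 and 1.68–1.91 points for one, two and three courses. In that model the all-randomised difference also falls, to 1.51–1.61 where it was recorded. Selection into strata cannot cause that, so those figures mix selection with treatment cut short. The protocol does not say whether improvement freezes. With selection isolated, the full scenario shows no steady rise by course.
- *It will create a false efficacy signal.* With no treatment effect the strata stay balanced. In the scenarios run, the bias shrinks a real effect.
- *It undermines the primary result.* This point does not touch the intention-to-treat comparison in all randomised patients.

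Nor is treatment length set by TCSS alone, since adverse events and drop-out for personal reasons also shorten it. Those too occur after randomisation, so they do not rescue the comparison.

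**Conclusion.** The point holds conditionally. The protocol's only named subgroup factor is undefined. On its natural reading it is a consequence of treatment and of the primary outcome, so arm comparisons within it lose randomised balance and are biased whenever treatment affects TCSS, as the trial assumes it does. In the scenarios examined, a uniform 2.0-point effect appears 0.04 to about 0.7 points too small, with the largest loss in the two-course stratum.

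Those sizes depend on assumed SDs, linear improvement and an outcome unaltered by stopping. The loss of randomised balance does not depend on the particular SDs. The matter is confined to a secondary analysis, but it should be settled before unblinding.

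**What to change.** Replace the subgroup sentence in Statistical analysis along these lines:

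- Arms will not be compared within strata of treatment duration or number of courses received.
- Any subgroup analysis will use baseline variables, for example the TCSS bands already given under Primary outcome measures (6–8, 9–11, 12–19), tested with a treatment-by-baseline-TCSS interaction.
- Number of courses received and time to TCSS below 6 will be reported by randomised arm in all patients. This answers the question about duration without breaking randomisation.

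If study phases were meant, say so instead and describe the analysis as a time-point comparison within the repeated-measures analysis.

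The cost is a short rewording and no new data, since applying the stopping rule already requires TCSS at the two-weekly visits. Separately, the two stopping statements in Study design leave a score of exactly 6 unassigned and must be reconciled by the sponsor, because reported course counts depend on how that score is handled.

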### Monitoring

This study will be performed in accordance with the approved protocol. An independent Data and Safety Monitoring Board (DSMB) will be formed before the trial start. The DSMB will review the data after 25%, 50%, and 75% enrollment to monitor the study progress and all adverse events (AEs) that may occur.

### Adverse events

All AEs will be recorded and any serious adverse events (SAEs) will be reported to the Research Ethics Committee (REC) within 24 h. When AEs occur, the study investigators will request that the patient terminate the foot bath and then determine whether this event was related to the investigational formula. The chief investigator may implement urgent safety measures to protect patients from immediate harm. If the AE is related to the investigational formula, it will be termed a side effect. If the side effect is mild and the patient agrees to commence, the foot bath treatment will continue after the symptoms abate. Patients will withdraw from the study if SAEs are observed.

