### Sample size

The primary outcome measure of the study is TCSS; hence, the sample size will be calculated based on preliminary TCSS results. We anticipate that TCSS scores will decrease 3.5 points in the TW foot bath group compared with 1.5 points in the control group [30, 31]. Based on a two-tailed type-1 error of 0.05 and a type-2 error of 0.099, we anticipate that 266 patients will need to be recruited for each group. Given the possibility of exclusion or lost follow-ups, an increase of 20% will be required for the sample size; therefore, 320 patients will be enrolled in each group.

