### Randomization

A block randomization sequence will be generated by SAS 9.2 software (SAS Institute Inc., Cary, NC, USA) with block size set at four, to be performed by an independent staff of the Key Unit of Methodology in Clinical Research (KUMCR) of Guangdong Provincial Hospital of Chinese Medicine. Eligible participants will be randomly allocated to either the experimental group or the control group at a ratio of 1:1 through the Central Randomization Management System developed by KUMCR. At each clinical site, randomization will be also performed at a 1:1 ratio to ensure even distribution.

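### The rule that patients leave the study after any serious adverse event, read plainly, ends outcome and safety observation and does not fit the follow-up promise or the all-randomised ITT analysis

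*Protocol article*

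**What the plan says.** Three sections of the protocol article bear on what happens to a patient after a serious adverse event (SAE).

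- **Adverse events.** For adverse events in general: "When AEs occur, the study investigators will request that the patient terminate the foot bath". Relatedness is then judged: "If the AE is related to the investigational formula, it will be termed a side effect". Treatment may resume after a mild side effect. The paragraph ends: "Patients will withdraw from the study if SAEs are observed".
- **Study design.** "All patients will be followed for three months after treatment". For those who leave early: "Patients who drop out due to side effects or personal reasons will be also followed up".
- **Statistical analysis.** The analysis is by intention to treat: "The ITT analysis will include all randomized patients".

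TCSS, the primary outcome, is assessed at baseline and at weeks 12 and 24 (Abstract). Study objectives places the primary comparison at the end of treatment and at the end of follow-up, and lists a comparison of side effects across the whole study as a secondary objective.

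**The concern.** Stopping an intervention and stopping observation are different decisions. The SAE sentence refers to the study. Earlier in the same paragraph, stopping the foot bath is described in its own words, so the SAE sentence is hard to dismiss as loose wording for a treatment stop.

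Taken at its word, the rule generates missing data. The trigger occurs after randomisation, may be caused by the allocated treatment, and may be associated with how the patient is doing. Data lost in that way cannot be assumed to be missing at random. The TCSS comparison could be biased if SAEs differ between arms, and the comparison of side effects would be cut short in patients who have already had a serious event. No analysis plan can recover visits that were never held.

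**Working it through.** **1. Setting the passages side by side.** A side effect, as the article defines it, is an event related to the formula. Two cases follow.

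| Case | Adverse events section | Study design, drop-out sentence | Study design, all-patients sentence |
|---|---|---|---|
| SAE related to the formula | leaves the study | followed up, if counted as a drop-out for a side effect | followed for three months |
| SAE not related to the formula | leaves the study | not named | followed for three months |

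The plain readings pull apart in both cases. In the second, only the general sentence about all patients supports continued follow-up. No section says that assessments continue after an SAE withdrawal.

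**2. Effect on the ITT set.** Membership is fixed by randomisation, so withdrawal removes nobody from the set. What would be missing is the later TCSS value, which the listed t-tests and repeated-measures ANOVA need.

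**3. How many patients.** The article gives no SAE rate, so 2% to 5% over 24 weeks is an assumption.

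- Both arms: 640 × 0.02 = 12.8 and 640 × 0.05 = 32, so about 13 to 32 patients.
- Per arm at 5%: 320 × 0.05 = 16. The allowance for exclusion and loss (Sample size section) is 320 − 266 = 54 per arm.

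These are upper bounds on patients missing at least one later TCSS. A patient whose first SAE falls after week 12 keeps the week-12 value.

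**4. Precision.** The figure of 266 cannot be reproduced directly because no SD is stated. Working backwards from the planned difference of 3.5 − 1.5 = 2.0 points, two-sided alpha 0.05 and power 1 − 0.099 = 0.901:

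SD = 2.0 × √(266/2) ÷ (z for two-sided 0.05 + z for power 0.901) ≈ 7.1

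With an SD of 7.1, n is 266 per group. The increase also reproduces: 266 × 1.20 = 319.2, rounded up to 320. If SAE losses came on top of the whole allowance, power would fall from 0.901 to about 0.893 at 3% and 0.887 at 5%. If they fall within the allowance, there is no loss against plan.

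**5. Bias.** Suppose patients with an SAE improve k points less than the others, with the same k in both arms. Leaving them out raises each arm's mean improvement by (SAE share × k), so the difference shifts by:

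shift = k × (SAE share in TW − SAE share in control)

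| Assumed shares, TW vs control | k = 1 | k = 3 | k = 3.5 |
|---|---|---|---|
| 5% vs 5% | 0 | 0 | 0 |
| 5% vs 2% | 0.03 | 0.09 | 0.105 |
| 10% vs 5% | 0.05 | 0.15 | 0.175 |

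The central case, 0.03 × 3 = 0.09 point, is 0.09 ÷ 2.0 = 4.5% of the planned difference. With more SAEs in the TW arm, the shift favours TW.

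**The case against.** The best defence is that the sections can be made to agree. Study design shows that leaving and being followed are compatible in this trial. If an SAE withdrawal is treated as a drop-out, treatment ends, follow-up continues and the patient is analysed as randomised. The SAE sentence closes a paragraph largely about stopping and resuming foot baths, which lends this reading some support. Withdrawal procedures and missing-data handling are also commonly left to a full protocol or SAP, neither of which is shown.

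Part of this stands. A reader might infer that the rules are flatly incompatible, but the documents do not prove that, because the lenient reading is available. It is not written down, however, and the drop-out sentence does not name SAEs unrelated to the formula, so sites could act differently. Nor is this a missing detail: it is a stated conduct rule that decides whether data are collected.

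A reader might also infer that the ITT analysis becomes impossible. It does not: withdrawn patients stay in the set, and the sample size already allows for loss.

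**Conclusion.** The point holds as a conflict in wording with a real consequence for data collection, and it should be fixed. It is not a must-fix. On its plain meaning, the SAE sentence ends observation by rule after an event that may be related to treatment. It sits badly with the follow-up commitments and weakens the all-randomised analysis by leaving outcomes unobserved.

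The size cannot be determined from the documents. The SAE rates, the imbalance between arms and the outcome gap used above are all assumptions. Under them the effect on the TCSS difference is small: zero with balanced SAEs and an equal gap, and about 0.1 point for 5% versus 2% with a 3-point gap. The stronger reasons to act are that the loss is avoidable and that it also reaches the safety comparison.

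Three stronger inferences are not supported:

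- **That the rule removes the sickest patients.** Nothing in the article links SAEs to TCSS severity.
- **That all safety information is lost.** The SAE itself is recorded and reported, and the DSMB reviews adverse events. Only what follows the SAE is at risk, and only on the plain reading.
- **That every SAE costs the primary outcome.** An SAE after week 12 leaves the end-of-treatment TCSS intact.

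**What to change.** Reconcile the Adverse events section with Study design and Statistical analysis by separating the end of treatment from the end of observation. State that after an SAE, whether or not it is judged related, the scheduled TCSS assessments at weeks 12 and 24 and the recording of adverse events continue unless the patient withdraws consent, and that the patient is analysed in the allocated arm. Whether foot baths stop or resume is a clinical matter for the sponsor and is not addressed here.

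The cost is a one-sentence amendment and a short note to sites. The visits are already scheduled, so they are kept rather than added. The article appeared in September 2018 with recruitment expected to run to December 2018, so at that point an amendment could still have protected later assessments. It could not restore visits already missed.

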## Discussion

The current clinical trial protocol has been designed as a large, multicenter, double-blind, randomized controlled study to evaluate the efficacy of TCM foot bath intervention for DPN treatment. As a common complication of diabetes, DPN occurs in approximately 60–70% of patients with diabetes mellitus worldwide. Diverse mechanisms are involved in the pathogenesis of DPN [32]. Glucose control plays a significant role in treating DPN, but is not adequate to prevent, arrest, or reverse damaged nerve function [33]. Several studies have demonstrated that pain medications have a beneficial effect on DPN symptoms but are limited by side effects [34]. It is challenging for physicians to implement a highly efficient and safe therapy for DPN [35]. Alternative therapies have been considered for DPN treatment due to their advantages of lower side effects and excellent efficacy. Herbal foot bath is an alternative therapy usually applied for DPN treatment_._ Herbs that promote circulation and eliminate stasis are believed to improve symptoms [36]. Although several studies have reported the efficacy of foot baths for DPN treatment, these studies were limited in scale and were not double-blind [37, 38].^.^ Our proposed clinical study should be the first large, multicenter, double-blind, randomized controlled study to assess the efficacy and safety of foot baths with TCM for DPN treatment.

DPN diagnosis is usually made with “the presence of symptoms and/or signs of peripheral nerve dysfunction in people with diabetes after exclusion from other causes” [39]. It requires the assessment of multiple features of neuropathy because DPN affects a variety of nerve fibers. The TCSS was proposed by diabetic and neuropathy scholars at Toronto, Canada in 2001. It is composed of three parts: a neurological symptom score; a nerve reflex score; and a sensory function examination score [24]. TCSS evaluates the severity of DPN using a scoring system: 6–8 points indicates mild neuropathy; 9–11 indicates moderate neuropathy; and 12–19 indicates severe neuropathy. Compared with other scoring systems, TCSS incorporates both symptoms and signs assessments and could therefore be considered more suitable and accurate for comparative studies.

An appropriate control group is critical for designing a high-quality clinical trial. Jiangyin Tianjiang Pharmaceutical Company was authorized to produce the formulas that are used in this clinical study. The control drug contains one-tenth of the dose that is contained in the TW formula; thus, it is difficult to distinguish the experimental and control drugs based on the color, external packing, or smell. To ensure that the formulas are more convenient to use, the herbs will be extracted and the liquid will be formed into granules that are soluble in hot water.

Another advantage of the proposed study is the use of intelligent thermostatic foot bath apparatuses that will be provided by the same supplier. Because some DPN patients have lost their local thermal sensation, they could easily scald their feet if the water temperature is too high or the foot bath time is too long. This intelligent foot bath device will maintain the water temperature at 42 °C and ensure that the bath lasts for 30 min. To avoid hygiene issues, each patient will be allocated his/her own foot bath device.

